## Abstract

**Introduction:**

In-bed cycling with patients with critical illness has been shown to be safe and feasible, and improves physical function outcomes at hospital discharge. The effects of early in-bed cycling on reducing the rate of skeletal muscle atrophy, and associations with physical and cognitive function are unknown.

**Methods and analysis:**

A single-centre randomised controlled trial in a mixed medical-surgical intensive care unit (ICU) will be conducted. Adult patients (n=68) who are expected to be mechanically ventilated for more than 48 hours and remain in ICU for a further 48 hours from recruitment will be randomly allocated into either (1) a usual care group or (2) a group that receives usual care and additional in-bed cycling sessions. The primary outcome is change in rectus femoris cross-sectional area at day 10 in comparison to baseline measured by blinded assessors. Secondary outcome measures include muscle strength, incidence of ICU-acquired weakness, handgrip strength, time to achieve functional milestones (sitting out of bed, walking), Functional Status Score in ICU, ICU Mobility Scale, 6 min walk test 1 week post-ICU discharge, incidence of delirium and quality of life (EuroQol Five Dimensions questionnaire Five Levels scale). Quality of life assessments will be conducted post-ICU admission at day 10, 3 and 6 months after acute hospital discharge. Participants in the intervention group will complete an acceptability of intervention questionnaire.

**Ethics and dissemination:**

Appropriate ethical approval from Metro South Health Human Research Ethics Committee has been attained. Results will be published in peer-reviewed publications and presented at scientific conferences to assist planning of future multicentre randomised controlled trials (if indicated) that will test in-bed cycling as an intervention to improve the physical, cognitive and health-related quality of life outcomes of patients with critical illness.

**Trial registration number:**

This trial has been prospectively registered on the Australian and New Zealand Clinical Trial Registry (ACTRN12616000948493); Pre-results.

Strengths and limitations of this studyThe randomised trial design with blinded assessments of skeletal muscle size, strength and function to provide objective measures of difference.The inclusion of an acceptability questionnaire will provide useful insights for subsequent implementation (if indicated).The study may not be powered for all secondary outcomes, and evidence of effect size from pilot data is not available for those measures.

## Background and rationale

Patients with critical illness often require mechanical ventilation for periods greater than 48 hours. It has been identified that skeletal muscle wasting occurs early and rapidly during the first week of critical illness.^1^ Despite international recommendations for patients with critical illness to commence activity as early as possible,^2^ it has been identified that exercise interventions are rarely initiated when a patient is on mechanical ventilation.^3^ This leads to prolonged immobility and may contribute to the development of intensive care unit-acquired weakness (ICUAW).^4^ In-bed cycling using a cycle ergometer has been proposed as a safe and feasible method of introducing early exercise for patients with critical illness on mechanical ventilation who are sedated and immobile, this includes patients requiring inotropic support.^5–7^ In-bed cycling may also assist in the preservation of muscle architecture. To date, only one randomised controlled trial (RCT) utilising in-bed cycling in the critically ill population has been published.^8^ This single-centre RCT (n=90) conducted in Belgium found in-bed cycling to be safe for patients with critical illness and to improve their 6 min walk distance, quadriceps force and Short Form-36 physical function scores on hospital discharge.^8^ A limitation of this study was that the effects of the intervention at the muscular level were not assessed with muscle biopsy or ultrasound.^8^ A pilot case-matched study of in-bed functional electrical stimulated cycling intervention in addition to usual care found positive physical outcomes observed among the cycling group including less time required to achieve functional milestones, time to stand and time to ambulate independently.^9^ In addition, a shorter duration of delirium among those who participated in the functional electrical stimulation (FES) in-bed cycling intervention was observed.^9^

A recent clinical trial has demonstrated that patients with critical illness may experience persistent weakness despite participating in intensive exercise programmes while they are critically ill.^10^ It has been suggested that intensive exercise programmes may not be effective if the commencement of these programmes is delayed.^11^ Early exercise commencement is intended to assist in the maintenance of muscle mass. This may be achieved through a moderation of the inflammatory process.^11^ Consequently, the effectiveness of exercise interventions that can commence early during critical illness are necessary to demonstrate if patient outcomes are improved by the early commencement of exercise during a period of critical illness.

Early clinical studies in the field have demonstrated potential for in-bed cycling interventions (with and without FES) to improve physical and cognitive function among patients with critical illness.^8 9^ There are currently no published RCTs investigating the effectiveness of in-bed cycling in patients with critical illness requiring prolonged mechanical ventilation on quadriceps structure, ICUAW and cognitive outcomes. Consequently, further investigation of the effect of in-bed cycling on muscle structure, physical function and cognitive function is warranted.

### Objectives

The objectives of this study are to:examine whether in-bed cycling in addition to usual care is effective in reducing the rate of rectus femoris cross-sectional area (CSA) atrophy and ICUAW in patients requiring more than 48 hours of invasive mechanical ventilation compared with usual care;investigate if in-bed cycling in addition to usual care is associated with better functional and cognitive outcomes in patients predicted to require more than 48 hours of invasive mechanical ventilation compared with usual care.

## Methods

### Study design and setting

This trial will be a two-arm, parallel RCT with individual participant allocation and blinding of the primary outcome assessor. It will be conducted in a 25-bed tertiary mixed medical and surgical adult intensive care unit (ICU) in Brisbane, Australia. Participants will be allocated 1:1 to receive either usual care or in-bed cycling in addition to usual care (figure 1). In designing this study, the^1^ SPIRIT 2013 Checklist was used to ensure that all recommended items in a clinical trial were addressed.^12^

**Figure 1 F1:**
[figure not shown]
Consort diagram giving flow of participants throughout the study. ICU, intensive care unit; n, number.

### Consent

It is anticipated that most patients who are eligible to participate in this study in the ICU setting will not be able to provide informed consent at the time of study enrolment. For those patients who may have the capacity to provide informed consent, the Richmond Agitation and Sedation Scale (RASS) will be used to determine if a patient is rated ’Alert and Calm'. If a patient is rated as ’Alert and Calm' on the RASS, the Confusion Assessment Method for the Intensive Care Unit (CAM-ICU) will be used to determine if a patient has had delirium within the preceding 24 hours. Provided a patient passes the RASS and CAM-ICU assessments, the treating clinical team will be approached to determine if the patient has the capacity to provide informed consent. Patients without delirium for the preceding 24 hours and deemed to have capacity will be approached to provide their own written informed consent for study participation. For eligible patients considered unable to provide informed consent at the time of study enrolment, substitute decision-makers (family members or next of kin) will be approached for written informed consent. The Queensland Civil and Administrative Tribunal (QCAT) has approved an application to provide consent for individuals who are unable to give consent and do not have a next of kin who is accessible to request consent on the patients’ behalf. Delayed consent from the patient will be sought once they can provide consent for themselves if they are enrolled using QCAT approval. Participation in the study is voluntary. Patients or their substitute decision-makers are able to withdraw at any time without any negative consequences on the care they would receive, their ongoing relationship with the hospital, or staff involved in their care.

The substitute decision-maker consent form (PICF_SDM_CYCLIST_V3.0_20160701) is attached as an online supplementary file 1.

10.1136/bmjopen-2017-017393.supp1Supplementary file 1

### Randomisation

Patients will be individually randomised in a 1:1 ratio to either intervention or usual care group. Blocking (random block sizes) will be used to help balance the groups. An investigator not involved in the screening, consenting, allocation or assessment processes will use computerised random number generation to create the randomisation sequence. A randomisation sequence will be uploaded onto the Research Electronic Data Capture (REDCap) secure web-based computer application.^13^ The REDCap randomisation module will reveal the group allocation of each patient to the intervention coordinator after a patient’s baseline data have been collected.

### Participants

The study aims to recruit 68 participants. Adult patients expected to require at least 48 hours of mechanical ventilation will be recruited, with the inclusion and exclusion criteria listed in table 1. Criteria to guide when to discontinue or not deliver an intervention are listed in box 1. Participants can be recruited into the study and baseline sonography measures performed if a patient does not currently meet the in-bed cycling safety criteria in box 1 (but are considered by their treating clinical team to be likely to meet the criteria within their stay in ICU).

**Table 1 T1:** Inclusion and exclusion criteria

Inclusion	Exclusion
Expected to require more than 48 hours of invasive mechanical ventilation	Pre-existing condition that is likely to impair mobility/mobility assessment (ie, significant neurological, musculoskeletal, cognitive or mental health disorder)
Able to provide consent or have a family member consent on their behalf	Neuromuscular disorder or acute primary brain lesion (ie, traumatic brain injury, intracranial haemorrhage, stroke or hypoxic brain injury)
Enrolled into the study within 96 hours of ICU admission	Injuries precluding cycle ergometry (ie, spinal/pelvic/lower limb orthopaedic injuries/open abdominal wound)
Expected to remain in ICU for more than 48 hours following study enrolment	Obesity >135 kg (MOTOmed Letto 2 maximum rated weight capacity)
	Uncontrolled seizures or status epilepticus
	Dire prognosis (ie, unlikely to survive the current admission)
	Pregnancy
	Children and/or young people (ie, <18 years)

ICU, intensive care unit.

Box 1Safety guidelinesActive or passive exercise should not be delivered if:Clinician’s opinion that patient’s condition is unstableResting HR<40 or >120 bpm or new arrhythmiaEvidence of coronary ischaemia, for example, chest pain or ECG changesMAP<60 or SBP>200 mm HgSpO_2_<90%RASS≥2Wounds of leg, pelvis or lumbar spine precluding cycle ergometryEvidence of active bleeding or coagulation disorder: INR>1.8, PLT<50 000/µL*Femoral vascular access†, for example, dialysis catheter, IABP, ECMO or lower limb arterial line‡Acute DVT or PEActive exercise should not be delivered if:>20 µg/min of norepinephrine or comparable inotropic or vasopressor supportFiO_2_>0.55 or PEEP>10 cmH2ORR>30 with adequate ventilatory supportTemperature >39°CStopping criteria: active or passive exercise should cease if:HR<50 or >140 bpm, or new arrhythmia develops (including ventricular ectopic or new-onset AF)Evidence of coronary ischaemia, for example, chest pain or ECG changesMAP<60 mm HgSBP>200 mm HgClinical signs of cardiorespiratory distressSpO_2_<90% for more than 1 minPatient’s request to stop therapy*Values outside this range would be tolerated if patient is therapeutically anticoagulated.†Other than femoral central line.‡If a femoral vascular access is inserted unilaterally the contralateral leg may be cycled unilaterally.AF, atrial fibrillation; bpm, beats per minute; DVT, deep vein thrombosis; ECMO, extracorporeal membrane oxygenation; FiO_2_, fraction of inspired oxygen; HR, heart rate; IABP, intra-aortic balloon pump; INR, international normalised ratio; MAP, mean arterial pressure; PE, pulmonary embolism; PEEP, positive end expiratory pressure; PLT, platelets; RASS, Richmond Agitation Sedation Score; RR, respiratory rate; SBP, systolic blood pressure; SpO_2_, saturation of peripheral oxygen.

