### Study intervention

All study patients will receive usual physiotherapy interventions while in intensive care. Physiotherapy interventions will include (but are not limited to): respiratory physiotherapy, physical rehabilitation exercise interventions including sitting on the edge of the bed, sit to stand transfers, sitting out of bed and walking. Usual care physiotherapy interventions will be prioritised over the in-bed cycling intervention. Safety guidelines (see box 1) will be used to determine if the intervention group patients are able to complete an additional daily 30 min progressive lower limb in-bed cycling using a bedside cycle ergometer (MOTOmed Letto 2). The lead physiotherapist ([name]) who has over 10 years of experience in rehabilitative exercise with patients with critical illness will primarily conduct the majority of in-bed cycling sessions. He has been trained by industry cycle ergometry representatives and has over 5 years of experience conducting in-bed cycling sessions with patients with critical illness. Experienced ICU physiotherapists trained in conducting in-bed cycling sessions may conduct the in-bed cycling sessions if the lead physiotherapist is unavailable. During the in-bed cycling exercise interventions, the patients’ vital signs will be monitored. If the intervention group patients are in a state of low arousal or sedated, they will cycle continuously and passively at the default passive speed of the cycle ergometer (20 revolutions per minute) for 30 min. When the participant is following commands, the clinician will verbally encourage the patient to complete in-bed cycling sessions actively for a duration of 30 min. Once the patient can cycle actively, the resistance applied by the cycle ergometer will be adjusted to facilitate patient intensity between 3 and 5 using the visual Borg scale rate of perceived exertion (category ratio 10),^14^ within the specified safety guidelines. An exercise intensity of 3–5 on the Borg rate of perceived exertion scale has been shown to be safe and feasible with patients with critical illness.^15^ This will enable the patient to cycle in-bed either passively or actively with assistance from the cycle ergometer. If a patient unexpectedly commences active cycling, the additional active in-bed cycling safety criteria will become relevant. If the patients are deemed unsuitable to continue active in-bed cycling, they will be asked to resume passive cycling. If the patient continues to actively cycle, the session will be ceased. The in-bed cycling sessions will continue until the patient completes a minimum of five in-bed cycling sessions, unless the patient is discharged from hospital prior to completing five sessions. The intervention will continue in the acute hospital ward if the patient is discharged from ICU prior to completing five in-bed cycling sessions. While the patient remains in ICU, in-bed cycling sessions will continue (up to 7 days/week), up to 28 days post-ICU admission. This frequency is congruent with usual physiotherapy services that can provide rehabilitative exercise interventions to ICU patients up to 7 days/week. Patients randomised to the usual care arm do not routinely complete in-bed cycling sessions during their hospitalisation. Any deviations from the planned protocol will be recorded to enable appropriate intervention description and, if indicated, a per-protocol analysis (in addition to the primary intention-to-treat analysis).

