### Trial management

The principal investigator ([name]) will oversee the conduct and progress of the trial. The principal investigator will screen the daily admission to ICU lists and liaise with the treating medical teams to optimise participant enrolment. No interim analyses are planned. The principal investigator will ensure all research personnel are appropriately orientated and trained, oversee recruitment and report to a trial safety monitoring committee who will monitor the progress and conduct of the trial. The trial safety monitoring committee will include: a physiotherapist and researcher experienced in the safe conduct of clinical trials with physiotherapy interventions; the trial coordinator and principal investigator; a critical care nurse who is also experienced in the safe conduct of clinical trials in critical care settings; and two ICU medical consultants experienced with the safe conduct of clinical trials in ICUs. One of the ICU medical consultants is employed externally to the study site. The principal investigator will provide an update report to the safety monitoring committee on a monthly basis (and additional ad hoc reports if an adverse event occurs). Additionally, any serious adverse events will be reported to the approving Metro South Human Research Ethics Committee that is overseeing the study. During in-bed cycling sessions, participants will be monitored for adverse events that will be recorded on the session data collection form. Adverse events that are being monitored for are: line or airway dislodgement, increase in ventilatory support that persists longer than 5 min post exercise (eg, increase in positive end expiratory pressure or fraction of inspired oxygen), blood oxygen desaturation less than 88% for more than 1 min, increase in vasoactive or pain relief medication greater than 5 mcg/min, increase in systolic blood pressure greater than 180 mm Hg for more than 2 min, increase in heart rate greater than 140 bpm for more than 2 min, decrease in mean arterial blood pressure less than 60 mm Hg for greater than 2 min and decrease in heart rate less than 50 bpm for more than 2 min.

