The strengths of this study are the implementation of the in-bed cycling intervention as soon as feasible (including while patients are still mechanically ventilated), with clear commencement and stopping rules. Another strength of the study is the blinded assessment of muscle structure, strength and function assessments. Measurement of the effect of early in-bed cycling on quality of life up to six months post ICU-admission is another strength that will assist to demonstrate if potential gains made early during a period of critical illness correspond to lasting functional improvements. It is expected that this study will also provide insights regarding the feasibility of the in-bed cycling intervention with patients with critical illness from the rates of compliance and completion of the in-bed cycling exercise intervention. The acceptability of in-bed cycling intervention from the perspective of patients with critical illness will be sought through a questionnaire and provide new information to inform potential implementation strategies for this intervention. A potential limitation of the study may be difficulty completing functional assessment measures at ICU discharge and at 1 week post-ICU discharge with patients who are either profoundly weak or present with an acute cognitive dysfunction. Further, usual care physiotherapy interventions will be delivered by treating teams independent of the study and prioritised over in-bed cycling. The frequency, intensity, type and duration of all usual care physiotherapy interventions are not being prospectively recorded as part of the trial outcomes. As the study design is an RCT, it is anticipated that the usual care physiotherapy will be similar across groups. Also this study is being conducted at a single centre and therefore results may need to be interpreted with caution.

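### Box 1 clears a resting heart rate of 40–49 bpm for cycling, but requires cycling to cease at any rate below 50 bpm

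*Protocol article*

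**What the plan says.** Box 1 (Safety guidelines, in the Participants section) has two lists that apply to active and passive exercise alike.

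- **Do not deliver:** the heart-rate item bars a session when the resting rate is below 40 or above 120 bpm, or when there is a new arrhythmia.
- **Cease:** the heart-rate item ends a session at "HR<50 or >140 bpm, or new arrhythmia develops". It sets no minimum duration and makes no reference to the patient's resting value.

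Under Study intervention, the Box 1 guidelines "will be used to determine if the intervention group patients are able to complete an additional daily 30 min progressive lower limb in-bed cycling". The box is therefore the working gate for each session.

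Trial management lists the adverse events watched for during sessions. One is a "decrease in heart rate less than 50 bpm for more than 2 min".

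The Discussion counts among the trial's strengths that cycling starts as early as feasible, "with clear commencement and stopping rules".

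**The concern.** A stopping limit normally lies at or outside the range in which starting is allowed, so that a patient who is fit to start is not already due to stop. The upper heart-rate limits follow that pattern; the lower ones are reversed.

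A therapist with a patient resting at, say, 45 bpm is told by one list that heart rate is no bar, and by the other that exercise at that rate must end. One therapist may withhold the session. Another may start it and stop almost at once. The article lets other trained physiotherapists run sessions when the lead is unavailable, so different staff may handle the same case differently.

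Two things are at stake. The first is a participant-safety rule that gives two answers for the same value. The second is the record of delivered treatment: the count towards the minimum of five sessions, the per-protocol requirement of at least 80% of sessions (minimum four), and the compliance and completion rates that the Discussion expects to report.

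**Working it through.** No sample-size, power or error-rate figure is involved, and the plan states no figure to reproduce. The check compares, for each quantity that appears in both lists of Box 1, the values that permit a start with the values that require a stop.

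**Heart rate**

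- Start permitted: not (HR < 40 or HR > 120), that is 40 ≤ HR ≤ 120.
- Stop required: HR < 50 or HR > 140.
- Both true at the lower end: 40 ≤ HR < 50. Testing each whole number from 20 to 200 bpm gives 40 to 49, which is 10 values. The ends are right: 40 is not below 40, and 49 is below 50.
- Both true at the upper end: none. The highest permitted start is 120 and stopping begins above 140, a margin of 140 − 120 = 20 bpm.

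**All paired numeric limits**

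| Quantity | Start permitted | Stop required | Values meeting both |
|---|---|---|---|
| Heart rate, lower | ≥ 40 bpm | < 50 bpm | 40–49 bpm |
| Heart rate, upper | ≤ 120 bpm | > 140 bpm | none |
| Mean arterial pressure | ≥ 60 mm Hg | < 60 mm Hg | none |
| Systolic pressure | ≤ 200 mm Hg | > 200 mm Hg | none |
| Oxygen saturation | ≥ 90% | < 90% for more than 1 min | none |

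**Does anything else in the article resolve the overlap?**

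- The saturation stop limit carries a duration; the heart-rate stop limit does not. Nothing tells the therapist to wait and see whether the rate rises.
- In the heart-rate stop item, the verb attaches to a new arrhythmia. The limit of 50 bpm stands as an absolute level, not as a fall from rest.
- The clinician may judge a patient unstable and withhold the session. That is a separate item, and a patient judged stable at 45 bpm is still cleared.
- No section exempts a patient whose resting rate is already between 40 and 49 bpm.

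**Route to the session counts**

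For a patient with the minimum of five sessions, the per-protocol threshold is 0.80 × 5 = 4 sessions. Suppose, as an assumption, that an aborted session counts as planned but not as received. One such session in five leaves 4/5 = 80%, which just qualifies; two leave 3/5 = 60%, which does not. How many patients this would touch cannot be worked out, because the article gives no distribution of resting heart rates.

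**The case against.** The strongest reply is that the two rules concern different states: one the resting rate, the other the rate during exercise. A patient whose rate rises promptly to 50 bpm or more leaves the conflict. The lists can also be obeyed in sequence, by starting and then stopping if the rate is still below 50, and this errs towards stopping. The box is offered as guidance and leaves room for clinical judgement.

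Much of this stands. A reader might infer that every patient in the band must be stopped the moment cycling begins, or that the box cannot be followed at all. The text supports neither. The conflict bites where the rate stays below 50 once cycling starts. It remains possible because patients in low arousal or sedated cycle passively at the machine's default speed, and nothing in the article says that this raises the rate.

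A reader might also infer that an unchanged resting rate of 45 bpm would be logged as an adverse event. The Trial management item is worded as a decrease lasting more than 2 min. An unchanged rate is not clearly a decrease, and a session stopped at once would not run that long. The item needs checking against the reconciled limits, but it does not plainly misfire.

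The effect on results is also limited. Sessions continue until at least five are completed, on the ward if need be, unless the patient leaves hospital first, so an aborted session need not lower the final count. Protocol deviations are recorded, and the primary analysis is by intention to treat.

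**Conclusion.** The contradiction is real and is confined to one limit: resting rates of 40–49 bpm satisfy the heart-rate criterion for starting and lie below the level at which exercise must cease. No other paired numeric limit in Box 1 conflicts, and no other part of the article settles this one.

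The consequence depends on the rate staying below 50 bpm after cycling begins and on no other item in the box keeping the patient out. The share of sessions affected cannot be estimated from the article; it is probably small. The intention-to-treat comparison of rectus femoris cross-sectional area is unlikely to move much. Any effect would show mainly in session delivery, adherence and membership of the per-protocol set.

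The case for correcting it rests on its being a participant-safety rule that is inconsistent as written, and one that the Discussion presents as clear. It does not rest on how often it would arise.

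**What to change.** The investigators and the safety monitoring committee should reconcile the start and stop heart-rate limits in Box 1, so that no value permitted at the start already meets the stopping criterion. They should then check that the 50 bpm adverse-event item under Trial management, worded as a decrease, is consistent with the reconciled limits. Which limit changes, and how, is a clinical decision for them.

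The cost is a short amendment to Box 1, with any matching change under Trial management and on the session data form. It needs no extra patients, visits or analyses.

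### As printed, the Box 1 footnote waives the platelet limit for therapeutically anticoagulated patients; it should apply to INR only

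*Protocol article*

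**What the plan says.** Under Methods, Participants, the article introduces the safety rules: "Criteria to guide when to discontinue or not deliver an intervention are listed in box 1". The first block of Box 1 lists conditions under which neither active nor passive exercise is given. One item in that block covers active bleeding or a coagulation disorder, with two laboratory limits: INR above 1.8 and platelets below 50 000/µL. An asterisk is printed straight after the platelet limit. The footnote to it reads: "Values outside this range would be tolerated if patient is therapeutically anticoagulated". It does not name INR and gives no lower platelet floor.

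The same section allows recruitment and baseline sonography "if a patient does not currently meet the in-bed cycling safety criteria in box 1", provided the treating team thinks the patient is likely to meet them during the ICU stay. Under Study intervention, the Box 1 guidelines "will be used to determine if the intervention group patients are able to complete an additional daily 30 min progressive lower limb in-bed cycling".

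**The concern.** Therapeutic anticoagulation is a sensible reason to accept a raised INR, which may simply be the intended drug effect. It is not a reason to accept a low platelet count: the drug does not account for that value, and the two together raise bleeding risk. As printed, a patient with platelets below 50 000/µL is held back when not anticoagulated but passes this limit when anticoagulated. That reverses the order of risk one would expect.

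What is at stake is the safety of individual cycling sessions. Physiotherapists other than the lead may run sessions, and sessions may continue on the ward after ICU discharge, so the written rule has to be right. No estimate, power figure or primary analysis depends on it.

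**Working it through.** There is no stated figure to reproduce. The check is a reading of the text plus a count.

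**Step 1. What the asterisk can cover.** The line has two limits and one mark, placed at the end.

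| Reading of the mark | INR above 1.8, anticoagulated | Platelets below 50 000/µL, anticoagulated |
|---|---|---|
| Last term only (platelets) | still barred | tolerated |
| Whole line | tolerated | tolerated |
| INR only (probable intent) | tolerated | still barred |

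The first two readings fit the printed position and wording, and both waive the platelet limit. The third would need the mark on INR or the word INR in the footnote, and neither is there. The next Box 1 item, on femoral access, shows that a mark can be put mid-line on a specific term: its dagger is placed that way.

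**Step 2. Whether another rule restores the limit.** Line breaks in Box 1 were lost in the text at hand, so items were separated by sense.

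- Items barring active or passive exercise: 10
- Items barring active exercise only: 4
- Stopping criteria: 7
- Total: 10 + 4 + 7 = 21. Items naming platelets: 1, the line carrying the asterisk.
- Table 1 exclusions: 8. Items naming platelets, coagulation or anticoagulation: 0.

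The waived limit is therefore the only platelet check in the article. Because patients may be enrolled before they meet Box 1, entry to the trial does not screen for it either; the check falls to Box 1 at each session.

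**Step 3. Whether later safeguards would catch the problem.** None of the 7 stopping criteria names bleeding. The adverse events monitored during sessions (Trial management) cover line or airway dislodgement, ventilatory support, desaturation, vasoactive or pain medication, blood pressure and heart rate. Bleeding is not listed. The pre-session coagulation line is the explicit bleeding safeguard, and it is the line the footnote loosens.

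**Step 4. Size.** With 68 patients allocated 1:1, 68 / 2 = 34 are planned for the cycling arm, and only they are exposed. The documents give neither the frequency of platelets below 50 000/µL with therapeutic anticoagulation nor a bleeding risk for in-bed cycling at any platelet count. No count of patients or sessions can be derived.

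**The case against.** The best counter-argument is that this is loose wording which no trained reader would apply literally. The asterisk ends the line, and end-of-line marks in this box can qualify a whole item: the double dagger in the femoral access item does so. The condition of the footnote, therapeutic anticoagulation, itself points to INR. Those applying the rule are a lead physiotherapist with over 10 years of rehabilitation experience in the critically ill, or experienced ICU physiotherapists trained in cycling. The footnote permits a session and does not demand one, and Box 1 is offered as guidance. Active bleeding, a clinician's view that the patient is unstable, and acute DVT or PE all still bar exercise; the last removes one group likely to be anticoagulated. A safety monitoring committee oversees the trial. If the waiver was deliberate, a team that keeps anticoagulation going at a low platelet count may already have weighed the bleeding risk.

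Most of this stands and limits the weight of the point. It does not make the printed rule right. Reading the mark as covering the whole line still includes platelets. A patient who is stable, not bleeding, anticoagulated and low in platelets meets none of the remaining bars just listed. The possibility of a deliberate waiver cannot be excluded from the text, but then the article should say so and give a floor. Nor is this a detail left to a fuller document: the threshold and its exception are both stated here.

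**Conclusion.** The point holds. As printed, the Box 1 exception removes the article's only platelet limit in patients who are therapeutically anticoagulated. It is a wording error in a safety rule that should be corrected, with small practical weight: it touches only the 34 patients planned for cycling, several other bars remain, and the primary outcome and its analysis are unaffected.

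The conclusion rests on the literal text of Box 1 and on the clinical premise that anticoagulation adds to bleeding risk when platelets are low. That an INR-only exception was intended is an inference that the document cannot confirm. The statement that no other platelet check exists applies to the article, since the full protocol is not at hand.

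**What to change.** Move the asterisk from the platelet limit to the INR limit, and reword the footnote to say that an INR above 1.8 is tolerated if the patient is therapeutically anticoagulated. Keep platelets below 50 000/µL as a bar to active and passive exercise whatever the anticoagulation status. If the investigators did mean to relax the platelet limit, they should state that and set a lower floor.

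The cost is one edited line, with no extra tests and no change to sample size or power. An occasional session may be withheld that the present wording would allow; the documents give no basis for saying how often.
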